## Abstract

**Background:**

Cancer survivorship rates have increased in developed countries largely due to population ageing and improvements in cancer care. Survivorship is a neglected phase of cancer treatment and is often associated with adverse physical and psychological effects. There is a need for broadly accessible, non-pharmacological measures that may prolong disease-free survival, reduce or alleviate co-morbidities and enhance quality of life. The aim of the Steps TowaRd Improving Diet and Exercise (STRIDE) study is to evaluate the effectiveness of an online-delivered physical activity intervention for increasing walking in cancer survivors living in metropolitan and rural areas of South Australia.

**Methods/Design:**

This is a quasi-randomised controlled trial. The intervention period is 12-weeks with 3-month follow-up. The trial will be conducted at a university setting and community health services in South Australia. Participants will be insufficiently active and aged 18 years or older. Participants will be randomly assigned to either the intervention or control group. All participants will receive a pedometer but only the intervention group will have access to the STRIDE website where they will report steps, affect and ratings of perceived exertion (RPE) during exercise daily. Researchers will use these variables to individualise weekly step goals to increase walking.

The primary outcome measure is steps per day. The secondary outcomes are a) health measures (anthropometric and physiological), b) dietary habits (consumption of core foods and non-core foods) and c) quality of life (QOL) including physical, psychological and social wellbeing. Measures will be collected at baseline, post-intervention and 3-month follow-up.

**Discussion:**

This protocol describes the implementation of a trial using an online resource to assist cancer survivors to become more physically active. It is an innovative tool that uses ratings of perceived exertion and daily affect to create individualised step goals for cancer survivors. The research findings may be of relevance to public health policy makers as an efficacious and inexpensive online-delivered intervention can have widespread application and may improve physical and psychological outcomes among this vulnerable population. Findings may indicate directions for the implementation of future physical activity interventions with this population.

**Trial registration:**

Australian New Zealand Clinical Trials Registry: ACTRN12613000473763.

## Background

The number of cancer survivors in Australia is increasing due to population ageing, growing incidence of some cancers and improvements in early detection and treatment [1]. However, cancer survivorship care is a neglected phase of the cancer care trajectory. The medical system tends to focus primarily on curing the cancer rather than managing the after-effects of treatment. Cancer and its treatments are often associated with adverse physical and psychological effects that can persist for months or years after treatment. Such after-effects can include fatigue, functional impairment, weight gain, sleeping difficulties and reduction in quality of life [2-7].

Increasing physical activity provides a non-pharmacologic strategy for the prevention and/or alleviation of many of these effects. Evidence has consistently indicated that physical activity has a positive impact on physiological outcomes (e.g. cardiovascular fitness, physical functioning, immune function, muscle strength, body composition, nausea and fatigue) and psychological wellbeing (e.g. mood, self-esteem, anxiety and depression) following a cancer diagnosis [8-13].

Despite these health benefits, many cancer survivors are not sufficiently physically active [14]. Cancer survivors living in rural and remote areas are at even higher risk of being physically inactive and experiencing negative effects after treatment than their urban counterparts [15,16]. This may be due to unique features of the rural environment including geographic diversity, social isolation, limited access to treatment services and facilities and the burden of travel distances [17]. Thus, there is a need for tailored, broadly accessible health promotion interventions to improve outcomes for survivors living in both metropolitan *and* rural areas.

The purpose of this paper is to describe the protocol of the STRIDE 12- week intervention, which has been specifically designed to test the effectiveness of an online resource for increasing regular walking and improving health and quality of life outcomes among cancer survivors living in metropolitan and rural areas. The trial also aims to identify whether there are region specific (metropolitan versus rural) predictors of successful engagement with the intervention. To our knowledge, it will be the first to use ratings of perceived exertion (RPE) and daily affect to deliver individualised, incremental step goals for participants relative to their baseline values.

### Theoretical framework

STRIDE is designed upon social cognitive theory which posits that physical activity interventions are most effective when they include intrapersonal mediators (including goal setting, self-monitoring and self-efficacy), social mediators (family and peer support), and environmental mediators (access to facilities and opportunities) [18-20]. Concepts from Locke and Latham’s [21] goal setting theory will also be integrated by encouraging 1) *goal acceptance* (participants will be provided with a workshop of the importance of active lifestyles thus placing importance on the achievement of their step goals); 2) *goal specificity* (step goals will be tailored to the individual taking into consideration their affect and level of physical capability); 3) *providing difficult goals* (step goals will be set high enough to encourage high performance but low enough to be attainable); and 4) *feedback* (a graph on the STRIDE website will show weekly step count averages over the 12 week program).

## Methods/Design

### Participants and setting

The STRIDE study is a quasi-randomised controlled intervention trial. Participants will be allocated to either the intervention group or the wait-list control group. Approximately 80 participants will be recruited and randomised by the research investigator(s). Table 1 shows the inclusion and exclusion criteria.

**Table 1 T1:** Inclusion and exclusion criteria

**Inclusion criteria**	**Exclusion criteria**
• Age over 18 years, no age limit higher	• Patient with metastasis,
• Have had cancer treated with curative intent (excluding skin cancer)	• Pregnant or intending to become pregnant during study period,
• Not undergoing active treatment (including chemotherapy and radiotherapy but will be included if taking long-term follow-up medications or therapies such as hormone therapy)	• Physical or psychological condition (i.e. cognitive decline) that may impede their participant in the study
• Permanent resident of South Australia,	
• Insufficiently active (engaging in less than 20 sessions of physical activity, one session lasting 30 minutes) over the past month determined by The Active Australia Survey [22]	
• Regular access to the internet (whether it be personal access or through a library or community centre)	
• Sufficient English language skills and cognitive ability to complete questionnaires,	
• Satisfy stage one of the pre-exercise screening guidelines for commencing exercise determined by the Sports Medicine Australia Pre-Exercise Screening System [23]	
• Approval by treating doctor to be part of the study,	
• Provide written informed consent	

### Study design and recruitment procedures

#### *Recruitment and screening*

The study flow is presented in Figure 1. Participants will be recruited via cancer support groups, newspaper advertisements, hospitals, flyers, government departments and allied health personnel contacts. Potential participants will firstly be screened by telephone to determine eligibility, and if eligible will be provided with further study information, a consent form and pre-exercise screening form, and asked to obtain medical clearance from their treating doctor using a standardised medical clearance form. Pre-exercise screening will be conducted using Stage 1 of the Sports Medicine Australia Pre-Exercise Screening System [23]. The first stage of the screening system is designed to screen out those people who are at a high risk for exercise-related complications due to underlying cardiovascular, cerebrovascular, respiratory or metabolic diseases and also pre-existing injuries. Upon completion and receipt of required consent and clearance forms by the research team, participants will be randomised into treatment conditions and contacted to make arrangements for study participation.

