### Randomisation and blinding

Participants will be randomly allocated to one of the two trial arms (intervention or wait-list control). A block design with allocation weight of 3:3 will be used to generate treatment allocation. It is not possible for three key researchers (LF, DZ, RS) to be blinded to participants’ group allocation as they will be performing the information sessions relevant to each group. It is not possible to blind participants to group allocation due to the nature of the intervention. Six other research assistants performing physical and questionnaire measurements will be blinded to the participants’ group allocation.

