### Protocol

All participants will attend two baseline workshops, one week apart. Each session will last approximately 90 minutes. At the first workshop, health measures will be taken (blood pressure, weight, height, waist and hip circumference) and fitness will be assessed using the 6-minute walk test. Participants will complete questionnaires about their physical functioning, quality of life and diet habits. They will be provided with a sealed pedometer (New-Lifestyles NL-1000 pedometer, New Lifestyles Inc., Lees Summit, MO) to wear for seven consecutive days (5 week days and 2 weekend days) which they will return at session two. At session two all participants will be provided with lifestyle information and a pedometer for use in the intervention (Yamax Digiwalker SW700). Those in the intervention group will be instructed on using the STRIDE website including how to log their steps and report their RPE and affect each day. On the basis of this information, they will be emailed weekly step goals which they will be encouraged to achieve. Following the 12-weeks of the intervention period, all measures will be repeated, and again after 6-months (i.e. 3-months post-intervention). At the conclusion of 6-months the control group will be offered the STRIDE program.

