### Outcome measures

Outcome measures will be assessed at three time points: baseline, end-program (week 13) and at the 3-month follow-up. The primary outcome is *daily steps*. Participants will wear a sealed pedometer (New-Lifestyles NL-1000 pedometer, New Lifestyles Inc., Lees Summit, MO) for seven consecutive days (5 week days and 2 weekend days), except for sleeping, showering, bathing, swimming or engaging in contact sports. Minimum wear time, as recorded by a log sheet, will be defined as 10 hours per day for four of the seven days, one of which must be a weekend day. The NL series pedometer has extensive empirical backing in the literature for validity and reliability, and displays the accuracy required to detect changes in step counts that are typical of walking interventions [43].

Secondary outcomes include:

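### Randomisation precedes the baseline week, and nothing says allocation is withheld until that week ends, so the baseline half of the primary change score is open to an allocation effect

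*Protocol article*

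**What the plan says.** Under Recruitment and screening, the trigger for randomisation is administrative: "Upon completion and receipt of required consent and clearance forms by the research team". No baseline measurement is required first. What follows directly from that trigger is that "participants will be randomised into treatment conditions and contacted to make arrangements for study participation".

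The Protocol section then describes what participation consists of: "All participants will attend two baseline workshops, one week apart". Workshop one takes the physical measures, the walk test and the questionnaires, and hands out a sealed pedometer "to wear for seven consecutive days (5 week days and 2 weekend days) which they will return at session two". Everyone receives lifestyle information and a second pedometer at session two. The only content described there as specific to one arm is the website instruction for the intervention group.

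Under Randomisation and blinding: "It is not possible to blind participants to group allocation due to the nature of the intervention". Three researchers are also unblinded because "they will be performing the information sessions relevant to each group". Against that, "Six other research assistants performing physical and questionnaire measurements will be blinded to the participants’ group allocation".

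Under Outcome measures, the primary outcome is daily steps, and "Outcome measures will be assessed at three time points: baseline, end-program (week 13) and at the 3-month follow-up". The Analytic plan tests steps with an independent-samples t-test on change scores. It also describes a mixed model with time (0, 12 and 24 weeks), group and their interaction, and commits to the intent-to-treat principle.

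**The concern.** A baseline value protects a comparison only if allocation cannot influence it. Here every baseline outcome is collected after allocation, in participants who are not blinded, and no stated step keeps the arm from them in the meantime. Someone who knows they are about to start a walking programme may walk more or less during the baseline week. Someone who knows they are wait-listed may answer quality-of-life or diet items differently, or not attend, since the programme is offered to controls only after 6 months.

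A change score subtracts baseline steps at full weight, so an arm-dependent shift in the baseline week appears in the estimated effect with nothing to dampen it. A randomised person who never reaches workshop one has no change score, which sits badly with the intent-to-treat commitment. Once baseline has been collected with the arm known, the analysis cannot separate an allocation effect from chance imbalance.

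**Working it through.** **Order of events**, from the sections Recruitment and screening and Protocol:

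1. Forms received; participant randomised.
2. Participant contacted to arrange attendance.
3. Workshop one: physical measures, walk test, questionnaires, sealed pedometer issued.
4. Seven-day baseline step count.
5. Session two: pedometer returned; website instruction for the intervention arm.

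All baseline outcomes (steps 3 and 4) follow randomisation (step 1). The remark under Step goals that the first week supplies baseline data concerns goal setting and does not move the outcome baseline ahead of randomisation.

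**Size.** The plan prints no figure to reproduce here, so this is an illustration.

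Inputs from the article: 41 per group (Sample size calculation) and alpha 0.05 (Analytic plan; two-sided assumed). Assumed: a shift of b SD in one arm's baseline steps that does not carry into follow-up; correlation rho between baseline and follow-up; equal SDs of 1; normal approximation.

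- Bias in the change-score contrast: b in absolute size.
- SD of change = sqrt(2(1 − rho)), which is 1 at rho = 0.5.
- SE = SD of change × sqrt(2/n) = 1 × sqrt(2/41) = 0.221.
- With λ = b/SE and no true effect, type I error = Φ(−1.96 + λ) + Φ(−1.96 − λ).
- With baseline as a covariate: bias = rho × b, SE = sqrt(1 − rho²) × sqrt(2/n) = 0.866 × 0.221 = 0.191 at rho = 0.5.

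| Assumed shift b | λ (change score, rho 0.5) | Type I, change score, rho 0.5 | Type I, change score, rho 0.7 | Type I, baseline as covariate, rho 0.5 |
|---|---|---|---|---|
| 0 | 0 | 0.050 | 0.050 | 0.050 |
| 0.1 SD | 0.45 | 0.074 | 0.090 | 0.058 |
| 0.2 SD | 0.91 | 0.148 | 0.215 | 0.082 |
| 0.3 SD | 1.36 | 0.274 | 0.418 | 0.123 |

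The 41 is the number recruited. If 20% are lost, 41 × 0.8 = 32.8, so about 33 per group remain. The change-score values at rho 0.5 are then 0.069, 0.128 and 0.230: a little lower because the test is less precise, with the bias itself unchanged.

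**Direction.** If the intervention arm walks more in the baseline week, its change is understated. For an assumed true effect of 0.6 SD at rho 0.5 and 41 per group, power is Φ(0.6/0.221 − 1.96) = 0.775 without a shift and Φ((0.6 − 0.2)/0.221 − 1.96) = 0.441 with a 0.2 SD shift. If instead the control arm walks more, or the intervention arm less, the effect is overstated.

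**Mixed model.** Time 0 is one of its levels. With complete data the interaction contrast of week 12 against week 0 is the difference in mean change, so it carries the same b.

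**The case against.** The strongest reply is that the article never says when participants learn their arm. Contacting them to arrange attendance is not the same as telling them their group. Workshop one is described identically for everyone, and the arms visibly part only at session two, when the sealed pedometer comes back. Disclosure at that moment would fit the text. The flow figure is not available to check, and this is a condensed article. This stands in part: a reader might infer that participants know their arm throughout the baseline week, and the text does not establish that. It does establish that allocation exists before baseline, with no stated safeguard in between.

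The mitigations also count. A sealed pedometer gives no step feedback, and blinded assistants take the physical and questionnaire measures. These limit feedback and assessor bias. They do not stop a participant who knows the arm from walking, wearing the device, answering or attending differently.

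Two stronger readings should be resisted:

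- A reader might set a 0.1 SD shift against a 0.60 SD design effect and call the bias 17% (0.1/0.6). The shift is an assumption. The 0.60 is not printed: it is back-calculated from 44 per group at 80% power, while the article states r of 0.30 to 0.50. Converting by d = 2r/sqrt(1 − r²) gives 0.63 to 1.15, so the same shift would be about 16% down to 9%.
- A reader might count withdrawals before baseline as extra to the 20% dropout allowance. The article does not restrict that allowance to losses after baseline. The mixed model could also use follow-up data from someone with no baseline count, although it would not remove a baseline shift.

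Finally, early allocation may have a practical purpose, since randomisation is tied to arranging attendance and some sessions are group-specific. That bears on the cost of the fix, not on the risk.

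**Conclusion.** The point holds as a risk built into the stated sequence, not as a demonstrated bias. Randomisation is fixed before every baseline outcome, participants are not blinded, concealment through the baseline week is not stated, and both the change-score test and the mixed model use that baseline.

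The size is unknown from the documents. Under the assumptions shown, with rho 0.5 and 41 per group, shifts of 0.1 to 0.3 SD give type I error of about 0.07 to 0.27. The upper values need shifts that nothing in the article supports or excludes, and the sign could be either. Covariate adjustment for baseline would shrink the bias without removing it. If allocation is in fact withheld from participants and session staff until the pedometer is returned, the reactivity concern largely disappears and a sentence saying so would settle it.

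**What to change.** Preferred: complete the workshop-one measures and the baseline pedometer week, then randomise at session two once the sealed pedometer is back and before the website instruction. The shift b is then zero by design, people who do not attend workshop one are never randomised, and the sample size is unaffected.

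Minimum: keep randomisation where it is, but state that allocation is concealed from participants and from the staff running the sessions until the pedometer is returned at session two, and name who holds the list until then.

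Cost: a scheduling change. Session-two rosters are fixed later, or the arms attend together and separate partway through that session.

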**Figure 1 F1:**
[figure not shown]
Flow of participants in study.

### Randomisation and blinding

Participants will be randomly allocated to one of the two trial arms (intervention or wait-list control). A block design with allocation weight of 3:3 will be used to generate treatment allocation. It is not possible for three key researchers (LF, DZ, RS) to be blinded to participants’ group allocation as they will be performing the information sessions relevant to each group. It is not possible to blind participants to group allocation due to the nature of the intervention. Six other research assistants performing physical and questionnaire measurements will be blinded to the participants’ group allocation.

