### Statistical considerations

#### *Sample size calculation*

A priori power calculations determined that a sample of 44 participants per group (n = 88) is needed to detect moderate effect sizes (r = 0.30-0.50) with 80% power and a significance level (alpha) of 0.05. Allowing for 20% dropout, 55 participants are required per group. Allowing for adjustment by baseline measure (r = 0.05) a total of 41 participants per group (n = 82) will be recruited.

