#### *Analytic plan*

Data will be entered and analysed using the IBM SPSS version 21 (SPSS, Inc, Chacago, IL) statistical software package. The intent-to-treat principle will be applied and the significance level will be set at 0.05. Baseline comparisons of demographic outcomes will be performed using independent samples t-tests. The primary outcome (number of steps/day) will be reported as independent samples t-tests comparing change scores in the two randomisation groups. Change scores for the secondary outcomes (health measures, diet quality and quality of life) will be calculated for each variable and compared between treatment and control groups using parametric or non-parametric procedures as appropriate for the data distributions.

Random effects mixed modelling will be used with time (0, 12, and 24 weeks) and group allocation (Intervention, Control) as the fixed factors. A time by group interaction term will be used to formally test the aims of the study.

Time by region (rural versus metropolitan) repeated measures ANOVA will be used to examine differences in the primary and secondary outcomes between groups over time. Sociodemographic factors and diet will be controlled for in the analysis.

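### Region is a stated aim, but the described allocation has no region stratum and the planned regional ANOVA names no treatment term

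*Protocol article*

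**What the plan says.** The protocol article brings region in at three points. The Abstract describes the study's purpose as "increasing walking in cancer survivors living in metropolitan and rural areas of South Australia". The Background adds a specific objective: "The trial also aims to identify whether there are region specific (metropolitan versus rural) predictors of successful engagement with the intervention". The Analytic plan then states: "Time by region (rural versus metropolitan) repeated measures ANOVA will be used to examine differences in the primary and secondary outcomes". The Background also treats region as relevant to activity: "Cancer survivors living in rural and remote areas are at even higher risk of being physically inactive".

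The design sections do not take this up. Under Randomisation and blinding, the scheme is "A block design with allocation weight of 3:3 will be used to generate treatment allocation", with no stratification factor named. In Table 1 the only geographic criterion is "Permanent resident of South Australia". Participants and setting gives a total of about 80, and Sample size calculation arrives at 41 per group (82); region plays no part in either. In the Analytic plan, the change-score t-test and the mixed model name group, or time and group. The regional ANOVA names time and region.

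**The concern.** A block design with one list controls the arm totals. It does not control the split within rural participants, who may be the smaller regional group. Three things follow.

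- **Engagement aim.** Only the intervention group uses the website, so only that arm informs region-specific predictors of engagement. How many rural participants it receives depends on chance as well as on recruitment.
- **Rural intervention-versus-control contrast.** An uneven split makes this contrast less precise.
- **Time by region analysis.** With no treatment term, an uneven rural split carries part of any treatment effect into the apparent regional difference. Even with a perfect split, the model as named shows whether the regions change differently on average over both arms, not whether the intervention works differently by region.

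**Working it through.** **Inputs.** From Sample size calculation: 41 per arm, 82 in total, 80% power, alpha 0.05 (two-sided assumed), 20% dropout. From Randomisation and blinding: 3:3 blocks, read as 1:1 in blocks of six. Assumed: the number of rural participants k, because the article does not give it.

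**Plan's own figure.** There is none for region. For the overall comparison, 2 × (1.96 + 0.842)² / 0.6² = 43.6, so the stated 44 per group corresponds to a standardised difference of 0.6. That value is used below. The later step from 55 to 41 per group is a separate matter; 82 is taken as stated.

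**1. Chance of rural imbalance.** If region plays no part in allocation, the rural number T in the intervention arm is close to hypergeometric: P(T = t) = C(k, t) × C(82 − k, 41 − t) / C(82, 41). Variance inflation of the rural contrast against an even split is (1/t + 1/(k − t)) / (4/k), averaged over t.

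| Rural k (assumed) | 60:40 or worse | 2:1 or worse | Mean variance inflation | Central 95% range of T |
|---|---|---|---|---|
| 12 | 0.349 (8:4 up) | 0.349 (8:4 up) | 1.10 | 3 to 9 |
| 20 | 0.441 (12:8 up) | 0.070 (14:6 up) | 1.04 | 6 to 14 |
| 30 | 0.252 (18:12 up) | 0.038 (20:10 up) | 1.02 | 11 to 19 |

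At k = 20 the chance of 13:7 or worse is 0.198. At k = 40 the chance of 60:40 or worse falls to 0.12. Simulating consecutive blocks of six (20,000 runs) gave 0.349, 0.448 and 0.258 for the 60:40 column, so the blocking hardly alters the result. At k = 12 no split lies between 7:5 and 8:4, so the two thresholds coincide.

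**2. Regional model without a treatment term.** Take k = 20 and a treatment effect of 0.6 SD.
- Split 12:8: 12/20 = 60% of rural and 29/62 = 46.8% of metropolitan participants are treated. The spurious regional difference is 0.132 × 0.6 = 0.08 SD.
- Split 14:6: 70% against 27/62 = 43.5%, giving 0.265 × 0.6 = 0.16 SD.
- The standard error of the regional difference is √(1/20 + 1/62) = 0.26 SD.

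**3. Main comparison.** Suppose change in steps differs between regions by 0.5 SD (assumed). A 12:8 split shifts the arm contrast by 0.5 × 4/41 = 0.05 SD and a 13:7 split by 0.5 × 6/41 = 0.07 SD, against a standard error of √(2/41) = 0.22 SD.

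**4. Is stratification what limits power?** Power = Φ(0.6/SE − 1.96) + Φ(−0.6/SE − 1.96), with 82 analysed and no baseline adjustment. At 20% rural with an even split there are 8.2 rural participants per arm, so SE = √(2/8.2) = 0.494 and power is 23%. For the group-by-region interaction, SE = √(2/8.2 + 2/32.8) = 0.552 and power for a 0.6 SD difference is 19%.

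| Rural share (assumed) | Rural-only, 1:1 | Rural-only, 2:1 | Interaction, 1:1 | Interaction, 2:1 |
|---|---|---|---|---|
| 20% | 23% | 21% | 19% | 18% |
| 30% | 32% | 29% | 24% | 22% |
| 50% | 48% | 44% | 27% | 25% |

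A 2:1 split costs about 1 to 4 points here. Perfect balance still leaves power low. For 80% rural-only power at 0.6 SD, about 2 × 44 = 88 rural completers would be needed, more than the whole trial.

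**The case against.** The strongest reply is that a journal article condenses a fuller protocol, and one sentence on allocation does not exclude stratification. That stands as a limit: the point concerns this text. It is still more than a missing detail, because the article states the aim, the allocation scheme and the regional model, and as described they do not fit together.

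The second reply is that regional balance at this sample size is optional, since the expected loss of precision is small and the 44% figure refers to 12:8, which inflates variance by only about 4%. This is correct and sets the size of the point.

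Three stronger readings are tempting, and the documents do not support them.

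- *The lack of stratification makes the regional aim unanswerable.* It does not. Power is low even with a perfect split, and the engagement aim depends on the rural count in the intervention arm. Stratification ties that count to about half of the rural enrolment but does not raise the enrolment.
- *Region is confounded with arm in the main comparison.* Chance imbalance after random allocation is not bias, and the test's error rate already allows for it. The Background's statement about region concerns level of inactivity, whereas the trial enrols only insufficiently active people and analyses change.
- *A rural minimum should be imposed and metropolitan enrolment closed once its share is filled.* With about 80 participants this could endanger the total, and the article gives no figures on which to judge the trade-off.

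The ANOVA sentence also refers to differences between groups, which could mean the trial arms. The factors it names are still only time and region.

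**Conclusion.** The point holds as a modest, inexpensive design improvement. As described, neither the allocation nor the regional ANOVA supports the regional objective as well as it could. Depending on an assumed 12 to 30 rural participants out of 82, a rural split of 60:40 or worse has a chance of 25% to 44%, and one of 2:1 or worse a chance of 4% to 35%. Expected precision loss in the rural contrast is about 2% to 10%. If the regions enrol in nearly equal numbers, the imbalance risk is smaller still.

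The main intervention-versus-control comparison remains unbiased, provided that allocation within blocks is random as the Randomisation section says. The limited power for regional questions comes mainly from the total and rural numbers. The more consequential gap is analytic: without a treatment term, the regional model cannot show whether the intervention's effect differs by region.

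**What to change.** 1. Classify each participant as metropolitan or rural before randomisation, by a stated definition. State residence alone does not give this; the address could be taken at telephone screening or with the consent forms.
2. Generate two 1:1 block lists, one per region. With blocks of six the rural arms can then differ by at most 3. With 20 rural participants (three full blocks and two people over), the intervention arm receives 9 to 11 of them instead of a likely range of 6 to 14.
3. Include region as a factor in the between-arm model.
4. Add group and group-by-region (by time) terms to the regional analysis. Describe it and the engagement analysis by region as exploratory, and report the rural numbers per arm.

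The cost is a second allocation list and one extra factor in the main model. With two lists, the overall arm totals could differ by up to 3 + 3 = 6 instead of 3, which is negligible for power. Sample size does not change. If allocation has already begun, steps 3 and 4 can still be adopted and deal with most of the analytic problem.
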